#### GSLT-PAQ

This self-report survey will be used to assess perceived PA participation [47].

Increasing total scores in the GSLT are associated with increased exercise behavior. Participants’ total GSLT scores can determine activity classification as either active or insufficiently active. Corresponding to the American College of Sports Medicine PA guidelines, 24 units or more are classified as active (meeting PA guidelines), 14-23 units as moderately active (not meeting PA guidelines), and 13 units or fewer as insufficiently active [47]. See Figure 2 for the sequence of outcome measures.

### Statistical Data Analysis Plan

All analyses will be conducted using 2-sided tests with a significance level of α=.05. Descriptive statistics will summarize participant characteristics and study variables. Continuous variables will be summarized using means and standard deviations or medians and interquartile ranges, as appropriate, and categorical variables using frequencies and percentages. Prior to inferential analyses, assumptions of normality, linearity, homoscedasticity, and absence of multicollinearity will be evaluated. If the assumptions for parametric analyses are not met, appropriate nonparametric or robust analytic methods will be applied.

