#### Aim 1: Construct Validity and Reliability of PROMIS-PF

Construct validity of the PROMIS-PF will be examined using a hypothesis-testing framework with related indicators of health and physical functioning consistent with COSMIN (Consensus-Based Standards for the Selection of Health Measurement Instrument) recommendations [59,60]. Predefined hypotheses were specified regarding both the expected direction and magnitude of associations. PROMIS-PF scores (higher scores indicate better perceived physical function) are expected to demonstrate:

Moderate-to-strong positive correlations with other self-reported measures of physical function (eg, LEFS and PROMIS Global Health; r≈0.50-0.70)Moderate positive correlations with habitual PA (steps/day; r≈0.30-0.50)Small-to-moderate negative correlations with comorbidity burden and fall risk indicators (r≈−0.20 to −0.50), where higher scores reflect poorer status.

Associations will be examined using Pearson correlation coefficients when parametric assumptions are met and Spearman rank correlations when assumptions are violated. Correlation coefficients will be reported with 95% CIs, and the interpretation will emphasize agreement with a priori hypotheses [60]. Correlations between PROMIS-PF and other self-report instruments (eg, LEFS and PROMIS Global Health) will be interpreted with caution, as these comparisons are subject to shared method variance, which may inflate associations due to common response tendencies rather than true construct overlap. Accordingly, these analyses will be considered supportive but weaker evidence of convergent validity.

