An a priori power analysis was conducted using G*Power (version 3.1.9.7; Heinrich Heine University Düsseldorf) [63]. Assuming a 2-tailed α=.05 and power=0.80, a total sample size of N=155 provides adequate power to detect small-to-moderate correlations (r ≥ 0.25-0.30), consistent with expected construct validity effect sizes. PROMIS-PF scores are expected to demonstrate moderate positive correlations with habitual PA and performance-based functional measures and moderate-to-strong positive correlations with other self-reported function scales. Negative correlations are anticipated with fall risk indicators and comorbidity burden. In addition to the power-based justification, precision was considered. At N=155, correlation estimates are expected to have reasonably narrow 95% CIs, supporting adequate precision in estimating associations [64].

The sample size for reliability analyses was informed by Borg et al [59]. Assuming 2 repeated measurements per rater, a subsample of n=25 is expected to provide sufficient precision to estimate ICC values ≥0.75, consistent with recommendations for reliability studies.

The full sample (N=155) will be used for primary construct validity analyses, while the nested subset (n=25) will support exploratory performance-based validity analyses and reliability estimation.

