#### Aim 2: Racial and Ethnic Disparities in Physical Function, PA, and QoL

To examine racial and ethnic disparities in physical function, PA, personal and environmental factors, and QoL among adults with ASD, analysis of covariance models will be used to compare adjusted mean outcomes between non-Hispanic White participants and participants from racial and ethnic minoritized groups. Covariates such as sex and autism severity will be included as appropriate to reduce confounding. If analyses are expanded to include more than 2 racial and ethnic groups, omnibus models will first be conducted, followed by multiplicity-adjusted pairwise comparisons where the overall test is statistically significant. Effect sizes and 95% CIs will be reported alongside *P* values. The planned sample size of 155 participants is expected to provide adequate power to detect medium-sized effects and to generate preliminary disparity estimates for future studies [63].

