### Recruitment

Of 544 adults with ASD contacted through the SPARK Registry, 229 responded to invitation emails, and 227 expressed interest in participating (see Figure 3). Following the eligibility screening, 15 individuals were excluded, resulting in 212 eligible participants. Of these, 203 were invited to participate, and 155 ultimately provided electronic informed consent and were enrolled in the study. Among enrolled participants, 101 (65.2%) identified as female, 53 (34.2%) identified as male, and 1 (0.6%) selected rather not to say.

The sample was racially and ethnically diverse: 79 (51.0%) participants identified as Black/African American, 40 (25.8%) as Hispanic, 34 (21.9%) as non-Hispanic White, 1 (0.6%) as Asian, and 1 (0.6%) did not report race/ethnicity. Table 2 presents the participant demographic characteristics.

**Table 2 table2:** Sex and race/ethnicity of enrolled participants (N=155).

Sex	Non-Hispanic White, n (%)	Black/African American, n (%)	Hispanic, n (%)	Asian, n (%)	Did not report, n (%)	Total, n (%)
Male	9 (17.0)	19 (35.8)	25 (47.2)	0 (0.0)	0 (0.0)	53 (34.2)
Female	25 (24.8)	60 (59.4)	14 (13.9)	1 (1.0)	1 (1.0)	101 (65.2)
Rather not to say	0 (0.0)	0 (0.0)	1 (100.0)	0 (0.0)	0 (0.0)	1 (0.6)
Total^a^	34 (21.9)	79 (51.0)	40 (25.8)	1 (0.6)	1 (0.6)	155 (100.0)

^a^Values in the total row and column are presented as n (% of the total sample). Percentages may not sum to 100 because of rounding.

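### Assumption checks decide whether the Aim 2 ANCOVA is kept, and nothing obliges its replacement to keep the covariates or the adjusted mean difference

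*Protocol article*

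**What the plan says.** The opening paragraph of the Statistical Data Analysis Plan sets one rule for all aims. It begins with the check: "Prior to inferential analyses, assumptions of normality, linearity, homoscedasticity, and absence of multicollinearity will be evaluated". It then gives the consequence: "If the assumptions for parametric analyses are not met, appropriate nonparametric or robust analytic methods will be applied". The error rate is fixed in the same paragraph: "All analyses will be conducted using 2-sided tests with a significance level of α=.05".

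The Aim 2 section commits to a specific target: "analysis of covariance models will be used to compare adjusted mean outcomes between non-Hispanic White participants and participants from racial and ethnic minoritized groups". Sex and autism severity are named as covariates to control confounding, and effect sizes with 95% CIs are to be reported. A comparison of more than two groups is optional. If made, it runs through an omnibus test and then multiplicity-adjusted pairwise comparisons.

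For Aim 1 the substitute is named: "Associations will be examined using Pearson correlation coefficients when parametric assumptions are met and Spearman rank correlations when assumptions are violated". For the Aim 2 ANCOVA and the Aim 3 regressions no substitute is named.

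The Recruitment section of the Results gives the group sizes: "79 (51.0%) participants identified as Black/African American, 40 (25.8%) as Hispanic, 34 (21.9%) as non-Hispanic White".

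**The concern.** The same data that are to be analysed decide which method is used, and the options differ in what they estimate. A robust method can keep the adjusted mean difference. The common nonparametric two-group test cannot: it takes no covariates and does not estimate a mean difference. The wording allows either, outcome by outcome, after the data have been seen.

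The rule also gives non-normality the same weight as unequal variance. With about 150 participants, non-normal errors do little to the validity of an adjusted mean comparison. Unequal variance between groups of very different size does matter, and a preliminary check removes only part of that problem. At stake are the error rate and the comparability of the disparity estimates that the study wants to hand on to larger studies.

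**Working it through.** **Inputs from the document.** Two-sided α=.05; N=155; 34 non-Hispanic White; 79 Black and 40 Hispanic, so 79 + 40 = 119. From Table 2, males among those stating sex: White 9/34 = 26%, Black 19/79 = 24%, Hispanic 25/39 = 64%; Black and Hispanic pooled (19 + 25)/(79 + 39) = 44/118 = 37%.

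**Assumptions, because the document gives no figures.** Skewness of errors 0.5 to 2 (gamma), with a lognormal extreme of 6.2; White SD 1.25 to 1.6 times the others; sex effect 0.3 to 0.8 SD; autism-severity imbalance 0.3 to 0.5 SD.

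**The plan's own figure.** The plan states no error rate for the switching rule. Its stated sample-size claim is "Assuming a 2-tailed α=.05 and power=0.80, a total sample size of N=155 provides adequate power to detect small-to-moderate correlations (r ≥ 0.25-0.30"). With power = Φ(atanh(r)·√(N−3) − 1.96), r=0.25 gives Φ(0.2554 × 12.33 − 1.96) = 88% and r=0.30 gives 97%. The claim holds and is not in dispute.

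**1. How often would a normality check fail?** The document names no test. Taking Shapiro-Wilk at 5% (4,000 simulated samples per setting; raw outcome n=155, ANCOVA residuals 34 vs 119):

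| Skewness | Raw outcome | Residuals | ANCOVA type I error |
|---|---|---|---|
| 0.5 | 59% | 55% | 4.7% |
| 0.75 | 93% | 89% | 5.2% |
| 1 | 99.7% | 99.5% | 5.2% |
| 1.5 | 100% | 100% | 5.0% |
| 2 | 100% | 100% | 4.2% |

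At skewness 6.2 the ANCOVA type I error is 4.4%. A formal check would therefore often reject where the adjusted comparison of means is still valid.

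**2. Unequal variance.** Let the White SD be k times the others, with no group difference, and ignore covariates.
- True variance of the difference: k²/34 + 1/119.
- Variance used by the model: [(33k² + 118)/151] × (1/34 + 1/119).
- k=1.25: true 0.05436, model 0.04246; SE ratio √1.280 = 1.131; type I error 2[1 − Φ(1.96/1.131)] = 8.3%.
- k=1.6: true 0.08370, model 0.05071; SE ratio √1.651 = 1.285; type I error 2[1 − Φ(1.96/1.285)] = 12.7%.

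Simulation with the Table 2 counts (34 vs 118 with sex stated, adjusted for sex) agrees and compares the options for k = 1.25 to 1.6:

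| Procedure | Type I error |
|---|---|
| ANCOVA, no remedy | 8–13% |
| Variance check, then HC3 if it fails | about 6–7% |
| Unadjusted Mann-Whitney if Shapiro-Wilk fails | 7–16% |
| HC3 throughout | about 5–6% |

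HC3 replaces the model variance by (X′X)⁻¹X′ diag[eᵢ²/(1−hᵢ)²] X(X′X)⁻¹, where e is the residual and h the leverage. With equal variances it holds 5.0% to 5.5% for skewness 0.5 to 6.2.

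**3. If the replacement were an unadjusted rank test, variances equal.**
- Planned two-group contrast: the sex mix differs little (26% vs 37% male), and false positives stay at about 5% to 6%.
- The same contrast with an autism-severity imbalance of 0.3 SD: 7.5% to 12%; with 0.5 SD: 12% to 25% (severity-outcome slope 0.3 to 0.5). ANCOVA stays at about 5%. The document does not report severity by group.
- Optional three-group expansion, with a Kruskal-Wallis gate and Holm adjustment, at sex effects of 0.3, 0.5 and 0.8 SD: Black vs Hispanic 3.7%, 8.9%, 19.9%; White vs Hispanic 2.9%, 5.8%, 11.7%.

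**The case against.** The strongest reply is that most of the harm comes from procedures the article does not prescribe. Assumptions are to be evaluated, which may mean residual plots. Robust methods are expressly allowed, and HC3 is one of them. Aim 2 commits to adjusted means with covariates, so a fallback that drops both is a strained reading of an appropriate method. The Missing Data section requires departures from the primary plan to be documented and justified. Fallback details often sit in an analysis plan, which is not shown here. The study also describes its contribution as hypothesis-generating.

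Much of this stands. A reader might infer that the rule will fire for almost any skewed outcome. That needs a formal test, and even then the rate is only 55% to 59% at skewness 0.5. A reader might also infer that the plan is to use unadjusted rank tests. It is not; the text merely fails to exclude them. Nor can one say that skewness is harmless everywhere. For a Pearson correlation of 0.40 between two skewed variables, coverage of the 95% CI falls from 93% to 74% as skewness rises from 0.95 to 6.2. The Aim 1 Pearson/Spearman rule is therefore left out of this point. No harm was computed for Aim 3, where a two-group rank test could not replace a regression with interactions.

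What remains is more than a missing detail. The stated rule is check-then-switch, it does not protect the Aim 2 estimand, and even its most charitable reading leaves about 6% to 7% where a fixed robust analysis gives about 5% to 6%.

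**Conclusion.** The point holds as a minor one. The rule lets preliminary checks choose the Aim 2 method and does not tie the replacement to the adjusted mean difference. On the charitable reading (check, then robust standard errors) the excess type I error is about 1 to 2 percentage points above nominal. If unequal variance went unremedied, type I error would be 8% to 13%. Both figures rest on an assumed White SD of 1.25 to 1.6 times the others. If the smaller group were instead the less variable one, ANCOVA would be conservative (0.8% at an SD ratio of 0.5, against 4.7% for HC3).

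The rank-test figures are conditional on a reading that the text permits but does not state. Through sex imbalance they concern only the optional contrasts that take the Hispanic group on its own. There, false positives are about 4% to 20% (Black vs Hispanic) and 3% to 12% (White vs Hispanic), for assumed sex effects of 0.3 to 0.8 SD.

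**What to change.** For continuous Aim 2 outcomes, and for consistency the Aim 3 regressions, make the covariate-adjusted linear model with HC3 standard errors the primary analysis, whatever the normality and variance checks show. Keep the checks as diagnostics for linearity and influential points. Report rank-based analyses, if wanted, only as sensitivity analyses that do not replace the adjusted mean difference. Leave the Aim 1 Pearson/Spearman rule as it is.

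The cost is about two sentences of analysis wording and one software option, with slightly wider intervals when variances are in fact equal. Data collection is complete but analysis is projected to run to July 2026, so the choice should be fixed and dated before the Aim 2 models are run.

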#### Aim 1: Construct Validity and Reliability of PROMIS-PF

Construct validity of the PROMIS-PF will be examined using a hypothesis-testing framework with related indicators of health and physical functioning consistent with COSMIN (Consensus-Based Standards for the Selection of Health Measurement Instrument) recommendations [59,60]. Predefined hypotheses were specified regarding both the expected direction and magnitude of associations. PROMIS-PF scores (higher scores indicate better perceived physical function) are expected to demonstrate:

Moderate-to-strong positive correlations with other self-reported measures of physical function (eg, LEFS and PROMIS Global Health; r≈0.50-0.70)Moderate positive correlations with habitual PA (steps/day; r≈0.30-0.50)Small-to-moderate negative correlations with comorbidity burden and fall risk indicators (r≈−0.20 to −0.50), where higher scores reflect poorer status.

Associations will be examined using Pearson correlation coefficients when parametric assumptions are met and Spearman rank correlations when assumptions are violated. Correlation coefficients will be reported with 95% CIs, and the interpretation will emphasize agreement with a priori hypotheses [60]. Correlations between PROMIS-PF and other self-report instruments (eg, LEFS and PROMIS Global Health) will be interpreted with caution, as these comparisons are subject to shared method variance, which may inflate associations due to common response tendencies rather than true construct overlap. Accordingly, these analyses will be considered supportive but weaker evidence of convergent validity.

Greater emphasis will be placed on the associations between PROMIS-PF and objective remote performance-based measures, which provide stronger evidence of construct validity due to reduced susceptibility to shared measurement bias. However, these comparisons are limited to a subset of 25 participants and will be interpreted as exploratory. These remote performance-based measures include the 5xSTS, the 30sSTS, and the Standing SLS test under EO and EC conditions. PROMIS-PF scores are expected to correlate negatively with 5xSTS completion time (r ≈ −0.40 to −0.70) and positively with 30sSTS repetitions and SLS duration (r≈0.40-0.70), such that better self-reported function corresponds to better observed functional performance and balance [44,60]. Given the smaller subsample, these analyses will be considered exploratory and interpreted with appropriate caution due to wider CIs. Adjustment for multiple comparisons will be applied within related families of analyses as appropriate.

Reliability will be evaluated for rater-derived scores from recorded remote performance assessments (ie, reliability of scoring rather than repeat participant testing). All sessions will be video-recorded and independently scored by 6 raters to estimate interrater reliability. To estimate intrarater reliability, each rater will re-score the same recordings after a 2-5-day interval. Intraclass correlation coefficients (ICCs) with 95% CIs will be calculated using absolute-agreement models appropriate to the rating design. ICC values will be interpreted using standard thresholds: ≥0.90 (excellent), 0.75-<0.90 (good), 0.50-<0.75 (moderate), and <0.50 (poor) [61-64]. We hypothesize that repeated ratings of recorded remote performance assessments will demonstrate strong interrater and intrarater reliability (ICC ≥0.80).

An a priori power analysis was conducted using G*Power (version 3.1.9.7; Heinrich Heine University Düsseldorf) [63]. Assuming a 2-tailed α=.05 and power=0.80, a total sample size of N=155 provides adequate power to detect small-to-moderate correlations (r ≥ 0.25-0.30), consistent with expected construct validity effect sizes. PROMIS-PF scores are expected to demonstrate moderate positive correlations with habitual PA and performance-based functional measures and moderate-to-strong positive correlations with other self-reported function scales. Negative correlations are anticipated with fall risk indicators and comorbidity burden. In addition to the power-based justification, precision was considered. At N=155, correlation estimates are expected to have reasonably narrow 95% CIs, supporting adequate precision in estimating associations [64].

The sample size for reliability analyses was informed by Borg et al [59]. Assuming 2 repeated measurements per rater, a subsample of n=25 is expected to provide sufficient precision to estimate ICC values ≥0.75, consistent with recommendations for reliability studies.

The full sample (N=155) will be used for primary construct validity analyses, while the nested subset (n=25) will support exploratory performance-based validity analyses and reliability estimation.

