## Introduction

### Background

Autism spectrum disorder (ASD) is a lifelong neurodevelopmental condition characterized by persistent differences in social communication and interaction, alongside restricted and repetitive patterns of behavior and interests [1]. Beyond these core diagnostic features, many autistic individuals experience clinically meaningful motor impairments, including reduced coordination, poor balance, atypical gait, and diminished muscle strength [2-5]. These impairments often persist into adulthood and across the life course [6-9], yet they remain relatively underrecognized in adult ASD research and clinical care. Motor limitations may reduce participation in physical activity (PA), increase sedentary behavior, and contribute to an elevated risk of falls, obesity, and chronic health conditions, ultimately affecting overall functioning and quality of life (QoL).

Despite their relevance, motor impairments and physical function remain underresearched in adults with ASD. These domains are not included in diagnostic criteria, are inconsistently assessed in clinical practice, and are infrequently addressed through movement-based rehabilitation strategies [2,10,11]. The limited use of standardized, objective measures of physical function in autistic adults also restricts the ability to evaluate intervention effects, monitor change over time, and tailor supports to individual needs [10]. This gap underscores a pressing need for accessible, valid, and reliable methods to assess physical function and motor performance in adults with ASD.

Barriers to health care access further complicate the evaluation and management of physical function in this population. Adults with ASD often encounter communication challenges, sensory sensitivities, anxiety, and limited provider familiarity with adult ASD, all of which may interfere with effective assessment and treatment [12-14]. These barriers are often compounded for racial and ethnic minority populations, who may also experience delayed diagnosis, underrecognition of co-occurring conditions, and structural inequities in care [15-17]. Additional barriers related to transportation, geography, financial constraints, and health system complexity may further reduce participation in clinic-based care [18-20]. Telehealth-based approaches may help address these barriers by reducing logistical burdens, minimizing sensory and social stressors, and expanding participation in both research and clinical services.

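### The rating-reliability conclusion rests on the ICC alone, which mixes scoring error with the spread of the 25 participants; scoring error in seconds or stands should be reported beside it

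*Protocol article*

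**What the plan says.** All of the following stands in the protocol article, under Aim 1: Construct Validity and Reliability of PROMIS-PF.

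- Interrater design: "All sessions will be video-recorded and independently scored by 6 raters to estimate interrater reliability".
- Intrarater design: "each rater will re-score the same recordings after a 2-5-day interval".
- Statistic: "Intraclass correlation coefficients (ICCs) with 95% CIs will be calculated using absolute-agreement models appropriate to the rating design".
- Reading of the result: "ICC values will be interpreted using standard thresholds: ≥0.90 (excellent), 0.75-<0.90 (good), 0.50-<0.75 (moderate), and <0.50 (poor".
- Hypothesis: "We hypothesize that repeated ratings of recorded remote performance assessments will demonstrate strong interrater and intrarater reliability (ICC ≥0.80".
- Size: "a subsample of n=25 is expected to provide sufficient precision to estimate ICC values ≥0.75".

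The same section limits the question to the reliability of scoring, and the Remote Video Assessment section rules out repeat assessment of participants. The article gives no measure of scoring error in the units of the tests and no SD for any test.

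**The concern.** The ICC is the between-person variance divided by the total variance. The same raters making the same errors get a high ICC in a varied group and a low one in a homogeneous group. With 25 participants, the label attached to the scoring method could be set by who happens to be in the subset.

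Four features of this study make that more than a textbook caution:

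- The Inclusion/Exclusion Criteria remove people whose health prevents them from rising from a chair or standing on either leg, which trims the low end.
- Bipedal and single-leg stances both stop at 45 seconds.
- The single-leg outcome is the best time over both legs and all trials, which pushes scores toward that cap.
- In the 30-second sit-to-stand test, needing the arms scores zero. This acts the other way, since one such participant adds a great deal of spread.

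So the hypothesis could fail with excellent raters or be met with ordinary ones. A reader of the results would also not learn how many seconds or stands apart two raters may be.

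**Working it through.** **Inputs from the article.** 25 participants, 6 raters, 2 scorings per rater, hypothesized ICC of at least 0.80, 95% intervals (z = 1.96). Test SDs are not given, so results are in SD units or rest on labelled assumptions.

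**The plan's own figure.** The article says that n = 25 gives sufficient precision for ICCs of 0.75 or more but states no target width, so there is no figure to reproduce. As context, the F-based (one-way) 95% CI for an observed ICC with n = 25 is:

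| ICC | 2 ratings | 6 ratings |
|---|---|---|
| 0.75 | 0.52 to 0.88 | 0.62 to 0.86 |
| 0.80 | 0.60 to 0.91 | 0.69 to 0.89 |

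**Scoring error at the hypothesized value.** Let SD be the total SD of a single rating.

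- Standard error of measurement = SD x sqrt(1 - ICC) = sqrt(0.20) = 0.447 SD.
- 95% limit for the difference between two ratings = 1.96 x sqrt(2) x 0.447 = 1.24 SD.
- Median absolute difference, if differences are normal = 0.6745 x sqrt(2) x 0.447 = 0.43 SD.
- The same 95% limit is 1.39 SD at ICC 0.75, 0.88 SD at 0.90 and 0.62 SD at 0.95.

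**Dependence on spread.** Set the total variance to 1 at ICC 0.80, so that the true variance is 0.8 and the error variance 0.2. Hold the error and multiply the true SD by m: ICC = 0.8m² / (0.8m² + 0.2). For illustration in seconds, assume an error SD of 0.4 s, so that m = 1 corresponds to a true SD of 0.8 s.

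| m | Assumed true SD | ICC | Band | 95% limit between two ratings |
|---|---|---|---|---|
| 0.5 | 0.4 s | 0.50 | moderate | 1.1 s |
| 0.75 | 0.6 s | 0.69 | moderate | 1.1 s |
| 1 | 0.8 s | 0.80 | good | 1.1 s |
| 1.5 | 1.2 s | 0.90 | excellent | 1.1 s |
| 2 | 1.6 s | 0.94 | excellent | 1.1 s |

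The last column is 1.96 x sqrt(2) x 0.4 = 1.11 s throughout: identical scoring, three different labels.

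**Capped stances.** If nearly all participants reach 45 s, the numerator of the ICC approaches zero. If every rating is 45 s, the ICC is 0/0 and undefined, although agreement is perfect.

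**Zero scores in the 30-second test.** Assume a mean of 14 stands, a true SD of 1 and an error SD of 0.7.

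- Without a zero: ICC = 1 / (1 + 0.49) = 0.67.
- With one zero among 25 on which all raters agree: between-person variance = [23 x 1 + (24/25) x 14²] / 24 = (23 + 188.16) / 24 = 8.80, and average error variance = 0.49 x 24/25 = 0.47.
- ICC = 8.80 / (8.80 + 0.47) = 0.95, although the other 24 are rated no better.

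**The case against.** The best reply is that these are general properties of the ICC and that the plan is sound within its scope. The 0.80 is a hypothesis, read beside a confidence interval and four bands. The absolute-agreement form already counts systematic differences between raters as error. Companion statistics are often left to a fuller analysis plan, and nothing in the article excludes them. All of that stands, and it is why this is not an error. It does not change the fact that the one yardstick the article fixes for its conclusion responds to participant spread as well as to rater error.

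It is also fair that 1.24 SD is a 95% limit, for single ratings, at an ICC of exactly 0.80; half of all differences would be within about 0.43 SD. The examples in seconds and stands use assumed SDs, so they show what could happen, not what will.

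A reader might go further and infer that the plan offers an ICC of 0.80 as proof that the tests can monitor individuals, and is wrong to do so. The documents do not support that reading. The Background remark that the present gap "restricts the ability to evaluate intervention effects, monitor change over time, and tailor supports to individual needs" describes the field and is not a study aim. Clinical and Research Implications mentions individualized care planning only as a possibility, and ties it to the relation between observed performance and patient-reported outcomes. Strengths and Limitations calls the contribution hypothesis-generating. Moreover, because all ratings are of the same recordings, neither the ICC nor any absolute error computed from them contains variation within a person from one session to another.

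**Conclusion.** The point holds as a specific, low-severity improvement. In the article shown, the conclusion on rating reliability rests on the ICC alone, and that figure can range from 0.50 to 0.94 with unchanged scoring error when the true between-person SD varies fourfold (0.5 to 2 times the value that gives 0.80). The risk is plainest for the capped stances, where a low or undefined ICC may go with near-perfect agreement.

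The 1.24 SD limit assumes a single-rating ICC of exactly 0.80 and roughly normal differences. How far spread will matter in these 25 people cannot be known from the documents, which give no test SDs. Nothing here shows that the raters will score poorly or that the hypothesis is badly chosen.

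**What to change.** Keep the ICC, its CI and the bands. From the same 25 x 6 x 2 = 300 ratings of each scored outcome, also report for each test, in seconds or stands:

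1. the standard error of measurement between raters and within raters;
2. the matching 95% limits of agreement, between and within raters.

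State that the rating-reliability conclusion will be drawn from these together with the ICC and its CI, so that a low ICC with small absolute error (as at the 45-second cap), or a high ICC driven by one or two extreme participants, is read correctly. Label these quantities, and any smallest detectable difference derived from them, as scoring error only, since participants are not retested. Present neither them nor the ICC as evidence for monitoring individuals.

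The cost is a few lines of code on variance components from ratings already planned, with no new ratings. The article projects completion of the analysis in July 2026, so the change can be written in before then.
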